## Background

The World Health Organization estimates that suicide accounts for over 800,000 deaths each year [1] and the lifetime prevalence of suicidal ideation is found to be 9.2%; i.e., in one in ten persons [2].

Different support options exist for people with suicidal thoughts. In Denmark, people at risk of suicide can receive free specialized psychosocial therapy in Suicide Prevention Clinics [3]. Some of these clinics have been operating since 1992, and the treatment seems to be effective [3]. Another support option is The Lifeline which provides free and anonymous support online and via telephone [4]. However, even in a high-income country like Denmark with various support options, the relatively stable suicide rate over the last 10 years indicates that not all people with suicidal thoughts seek or benefit from the existing support options. Internet-based therapy is still at a very early stage in Denmark. In 2016 only a couple of studies in Denmark were investigating the effect of the few Internet-based therapy programs that exist, but findings from other countries indicate that clinically and cost-effective online treatment options exist for depression and anxiety disorders [5, 6]. A Dutch randomized controlled trial found that an online self-help intervention for people with suicidal thoughts was effective in lowering suicidal thoughts and cost-effective [7, 8].

The objective of the Danish Self-help Online against Suicidal thoughts (SOS) trial is to examine whether an Internet-based self-help intervention, provided to people with suicidal thoughts, is superior to a waiting-list control condition in reducing suicidal thoughts. Key secondary outcomes of this study cover psychological wellbeing as well as costs related to health care utilization and production loss.

The study is a partial replication of the aforementioned Dutch trial [7]. While the previous trial excluded people with severe suicidal thoughts and did not extend the follow-up period to post treatment, the Danish trial aims to address these issues.

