#### Secondary outcome measures

Secondary outcomes cover psychological wellbeing and health care utilization as well as productivity level for paid and unpaid work. In addition, episodes of deliberate self-harm, death by suicide and the participant’s perception and experience of the intervention will be measured.

Level of suicidal thoughts will be measured using the Suicidal Ideation Attributes Scale; a newly developed scale for measuring suicidal thoughts consisting of five questions [7]. We will test the validity of the Danish version of the scale.

Depressive symptoms will be measured using the Major Depression Inventory and the six-item Hamilton Depression Rating Scale. The Major Depression Inventory is developed by the World Health Organization’s Collaborating Center in Mental Health and will be used to generate an *International Classification of Diseases*, *10th edition* (ICD-10) or a *Diagnostic and Statistical Manual of Mental Disorders*, *version 4* (DSM-IV) diagnosis of clinical depression based on the baseline measurement [13, 14]. The six-item Hamilton Depression Rating Scale is an abbreviated version of the original 17-item scale containing six core symptoms of depression [15]. It will be used to assess the severity of a depression [16]. Hopelessness will be measured using an established standard tool, the Beck Hopelessness Scale [17]. The Penn State Worry Questionnaire Past Week will be used to determine the participants’ level of worrying [18]. Quality of life will be measured with the WHO-5 Well-Being Index, which is a well-established and validated questionnaire [19].

Health care utilization registered in the Danish registers will be assessed. Every person in Denmark has a personal identifier that is listed in the Danish registers [20]. Health care utilization at somatic hospitals, outpatient clinics and emergency rooms will be collected from the National Patient Register. Data on contacts to the participant’s general practitioner will, together with services from psychologists or psychiatrists who are subsidized or partly subsidized by the authorities, be obtained from the National Health Service Register. Data on prescribed medication will be obtained from the National Prescription Registry.

Level of paid and unpaid work will be assessed using the Trimbos/IMTA questionnaire for Costs associated with Psychiatric Illness [21].

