### Statistical methods

The null-hypothesis assumption is that there is no difference between the intervention and the control condition with respect to suicidal thoughts and the secondary outcome measures. Linear mixed models with repeated measurements and an unstructured covariance matrix, will use measurements at baseline, 2, 4 and 6 weeks (post test) with the purpose of modeling changes over time in suicidal thoughts. Mixed models will also be used to assess the long-term effect at 6 months after post test as well as the effect on the participant’s level of depression. This analytical approach handles missing data appropriately using maximum likelihood, under the assumption that data are not missing-not-at-random. The analytical models will include baseline values and stratification variables. Changes in other secondary outcomes will be measured using ANCOVA with multiple imputations. The imputation models will be linear regression for scale variables and binary logistic regression for dichotomous variables. Imputation models will be constructed separately for each randomization group, and include baseline values of the scales in question, stratification variables, variables predicting missing data, and potential auxiliary variables identified for each outcome. Analytical models will include the stratification variables. Robustness of analyses using multiple imputations will be tested using sensitivity analyses instead, replacing missing data with either very low or very high scores for scale variables, and all 0s or all 1s for dichotomous data. Since no missing data are present for register data, imputations will not be necessary for these analyses. Cohen’s *d* test will be used to determine the difference between the intervention and the control condition. In addition, incidence rates of deliberate self-harm will be calculated using a self-report questionnaire and hospital records. A cost-effectiveness analysis will be conducted based on the health care utilization and productivity levels of the observed participants. Lastly, the participant’s evaluation, usage and experience of negative effects during the intervention will be calculated and described.

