### Sample size

The sample size was estimated based on the expected effect on suicidal thoughts at 6 weeks. In the Dutch trial, the pooled standard deviation at post test was 0.9 and an effect size of 0.28 (Cohen’s *d*) was observed. If the true difference in mean scores of the intervention and the control condition is 0.30 in the Danish trial, 175 participants in each condition are needed to reject the null hypothesis that there is no difference between the intervention and the control condition at post test on suicidal thoughts with probability (power) 0.8. The type I error probability associated with this test of the null hypothesis is 0.05.

Approximately 90% of participants in the Dutch trial completed all post-test questionnaires. Accounting for a dropout rate of 20%, a total of 438 participants will be needed.

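### The cost-effectiveness analysis rests on undefined observed participants; read naturally, this leaves out questionnaire non-responders whose register costs are known

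*Protocol article*

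**What the plan says.** The economic analysis is fixed in one sentence of Statistical methods: "A cost-effectiveness analysis will be conducted based on the health care utilization and productivity levels of the observed participants". The article does not say who the observed participants are.

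The two cost inputs come from different sources, both described under Secondary outcome measures. For utilization: "Health care utilization registered in the Danish registers will be assessed". For productivity: "Level of paid and unpaid work will be assessed using the Trimbos/IMTA questionnaire for Costs associated with Psychiatric Illness". Statistical methods says of the registers: "Since no missing data are present for register data, imputations will not be necessary for these analyses".

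The same section sets out how missing questionnaire data are handled elsewhere. For the mixed models of suicidal thoughts and depression: "This analytical approach handles missing data appropriately using maximum likelihood, under the assumption that data are not missing-not-at-random". For the rest: "Changes in other secondary outcomes will be measured using ANCOVA with multiple imputations", with imputation models built separately in each arm. Costs are not a side issue; the Background says: "Key secondary outcomes of this study cover psychological wellbeing as well as costs related to health care utilization and production loss".

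**The concern.** Of the analysis sentences in Statistical methods, only this one names a restricted population. It sits in a paragraph largely about missing data, where observed ordinarily means not missing. It also covers utilization and productivity together. A total cost needs both, so without imputation it cannot be formed for someone who did not return the productivity questionnaire. Such a person's hospital, general practice and prescription use would be known and yet left out.

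Two things are at stake. The first is selection. In a suicidal population, people who stop answering may differ in hospital contacts and work loss. The article also gives reasons why response could differ by arm: only the intervention arm has modules, reminders that a module has opened, the message system, and telephone tracing when someone stops following the program. Controls wait 32 weeks. The second is coherence. The mixed model draws on every recorded score, including scores from people who later stop answering, so a responder-only cost difference could be set against an effect estimated in a wider group.

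**Working it through.** **What each input allows**

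| Input | Source | Missing for non-responders? | Method given elsewhere in the article |
|---|---|---|---|
| Health care utilization | National registers | No, according to the article | None needed |
| Productivity | Self-report questionnaire | Yes | Multiple imputation by arm, as one of the other secondary outcomes |
| Suicidal thoughts (assumed effect measure; the article names none for this analysis) | Self-report scale | Yes | Maximum likelihood mixed model |

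Every input is either complete or already has a missing-data method. Only the cost-effectiveness sentence points to observed data instead.

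**1. The plan's own figure.** The article gives no number for the cost-effectiveness analysis, so the Sample size section supplies the scale: "Accounting for a dropout rate of 20%, a total of 438 participants will be needed".
- Per arm, two-sided 0.05, power 0.80, difference 0.30 in SD units: 2 × (1.960 + 0.842)² / 0.30² = 2 × 7.85 / 0.09 = 174.4, rounded up to 175.
- With 20% dropout: 175 / 0.80 = 218.75, rounded up to 219; 2 × 219 = 438.

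Both figures reproduce with 0.30 as a standardized difference. With the quoted SD of 0.9 the formula gives 142 per arm. That does not bear on the present point.

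**2. People left out on the ordinary reading (illustrative).**
- 20% non-response (the planned dropout): 438 × 0.20 = 87.6, about 88, leaving about 350.
- 10% non-response (from the roughly 90% post-test completion quoted for the Dutch trial): 438 × 0.10 = 43.8, about 44, leaving about 394.

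**3. Precision.** With the same variance per person, the standard error grows by √(randomized / analysed).
- At 20%: √(438 / 350) = 1.119, about 12% larger.
- At 10%: √(438 / 394) = 1.054, about 5% larger.

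Using everyone recovers this in full for the register component, and only in part for imputed productivity.

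**4. Bias.** Let d be an arm's non-response proportion and k the mean cost of its non-responders minus that of its responders, in SD units. The responder mean then lies d × k below the whole-arm mean, so the bias in the cost difference (intervention minus control) is −(d_I × k_I − d_C × k_C). The article gives no value for any of these. The following are assumptions, with k equal in both arms and running from 0.25 to 1.0:

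| Non-response, intervention / control | Size of bias (SD) |
|---|---|
| 20% / 20% | 0 |
| 25% / 15% | 0.10 × k = 0.025 to 0.10 |
| 30% / 10% | 0.20 × k = 0.05 to 0.20 |

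Equal non-response is not protective if the gap differs by arm. With 20% in both arms, k_I = 1.0 and k_C = 0.25, the bias is −(0.20 − 0.05) = −0.15 SD. The sign reverses if the arms swap roles or if non-responders cost less.

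**The case against.** The strongest reply is that the restriction is inferred. The article never says completers or responders, and never says that anyone's register costs are set aside. Since register data are complete, everyone is observed in that sense; the phrase may only mean that costs come from trial participants and not from a model. Production loss is a secondary outcome, so the planned multiple imputation arguably covers it already. The 20% is an allowance for the 6-week primary outcome, and no response rate for the productivity questionnaire is given. A condensed article may also leave economic detail to another document.

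Much of this stands. The exclusion is the natural reading of an undefined term, not an explicit statement, and the counts are illustrations. The benign reading still does not settle the matter, because the sentence covers productivity too, which is not observed for non-responders. Nor is this only omitted detail: the article does name a population, and in words that sit badly with its own account of the data.

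Two stronger readings are tempting and not supported. A reader might infer that the randomized comparison is abandoned. Nothing regroups participants; even a responder-only analysis would compare the arms as allocated. A reader might also infer that every other analysis keeps all randomized participants. The article declares no intention-to-treat set, leaves the analysis set for self-harm rates unstated, and only describes evaluation, usage and negative effects.

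**Conclusion.** The point holds as a defect of wording with a real analytic consequence. An undefined term permits, and on its ordinary reading prescribes, a cost-effectiveness analysis without questionnaire non-responders, although their register costs are known and the article already has a method for their missing productivity.

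The loss of about 44 to 88 people, with standard errors about 5% to 12% larger, assumes that 10% to 20% non-response carries over to the productivity questionnaire. Bias depends on quantities the article does not give: it is zero if d × k is equal in the two arms, and up to 0.20 SD in the scenarios assumed here. The primary analysis is unaffected.

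**What to change.** In the cost-effectiveness sentence, replace the reference to observed participants with all randomized participants, analysed by allocated arm. State that register costs are used for everyone, and that missing questionnaire productivity and effects are handled by the by-arm multiple imputation already planned, with register costs among the predictors. Keep the observed-case analysis as a sensitivity analysis and define its population.

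The cost is one revised sentence and a little more analysis work: the imputation model gains variables, and its results must be carried through to the cost-effectiveness estimate. No further data collection is needed.

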### Sample size

The sample size was estimated based on the expected effect on suicidal thoughts at 6 weeks. In the Dutch trial, the pooled standard deviation at post test was 0.9 and an effect size of 0.28 (Cohen’s *d*) was observed. If the true difference in mean scores of the intervention and the control condition is 0.30 in the Danish trial, 175 participants in each condition are needed to reject the null hypothesis that there is no difference between the intervention and the control condition at post test on suicidal thoughts with probability (power) 0.8. The type I error probability associated with this test of the null hypothesis is 0.05.

Approximately 90% of participants in the Dutch trial completed all post-test questionnaires. Accounting for a dropout rate of 20%, a total of 438 participants will be needed.

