### Outcomes

#### Primary outcome measure

The primary outcome is a reduction in suicidal thoughts, measured by the Beck Scale for Suicide Ideation. The 19-item self-report scale measures the severity of suicidal thoughts on a scale from 0 to 38 with a higher score indicating higher severity. The Beck Scale for Suicide Ideation is a validated and frequently used measure of suicidal thoughts [12]. As in the Dutch trial, a pre-post difference of 6 points is considered clinically significant [8].

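### The sample-size paragraph words 0.30 as a raw mean difference beside an SD of 0.9, but 175 per arm follows only if 0.30 is a Cohen's d

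*Protocol article*

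**What the plan says.** The Sample size section bases the calculation on suicidal thoughts at 6 weeks. It reports that in the Dutch trial "the pooled standard deviation at post test was 0.9 and an effect size of 0.28", the latter labelled as Cohen's d. The planning assumption comes next: "If the true difference in mean scores of the intervention and the control condition is 0.30 in the Danish trial". From this it derives 175 participants per condition to reject the null hypothesis "at post test on suicidal thoughts with probability (power) 0.8", and adds that "The type I error probability associated with this test of the null hypothesis is 0.05". It does not say whether the test is one- or two-sided. A 20% dropout allowance takes the total to 438.

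The section on the primary outcome measure describes the Beck Scale for Suicide Ideation: "The 19-item self-report scale measures the severity of suicidal thoughts on a scale from 0 to 38". Under Eligibility criteria, scores below 3 are excluded. Under Randomization, the sample is stratified at a score of 16 or more.

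**The concern.** A reader who takes the paragraph at its word has a mean difference (0.30), an SD (0.9), a power and a type I error rate. Those four numbers fix the sample size, and they do not fix it at 175. So the stated power does not follow from the stated inputs, in the only paragraph that justifies the number recruited.

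The SD adds a second difficulty. No unit is given, and the value looks very small for a score running from 0 to 38. Without a usable SD in scale points, nobody can say how large a between-group difference on the Beck scale the trial was designed to detect.

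**Working it through.** **Inputs (protocol article).** From Sample size: difference 0.30, SD 0.9, Dutch d 0.28, power 0.80, type I error 0.05, 175 per arm, dropout 20%, total 438, and about 90% post-test completion in the Dutch trial. From Randomization: 1:1 allocation. Assumption: a two-sided, unadjusted two-sample comparison of means.

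**Formula.** n per arm = 2 × (1.960 + 0.842)² / d², where d = difference / SD and (1.960 + 0.842)² = 7.849. Non-central t results are given as a check.

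**Step 1: reproduce the plan's figure.**
- With 0.30 read as Cohen's d: 2 × 7.849 / 0.30² = 174.4, rounded up to 175 (t-test 175.4).
- Dropout: 175 / 0.80 = 218.75, so 219 per arm and 438 in total. This step is correct.

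**Step 2: use the inputs as worded.**
- d = 0.30 / 0.9 = 0.333.
- 2 × 7.849 / 0.333² = 141.3, rounded up to 142 (t-test 142.2).
- Power at 175 per arm: 87.5% (t-test), not 80%.
- A one-sided 5% test moves further from 175: 112 per arm.

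**Step 3: find what makes 175 right.** Solving for the SD with a raw difference of 0.30 gives 1.00. Solving for the raw difference with SD 0.9 gives 0.27, which is again d = 0.30. Both say that 0.30 was used as a standardised effect.

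**Step 4: set the SD of 0.9 against the scale.** If 0.9 were in raw points, the entry threshold of 3 and the stratification cutoff of 16 would lie 13 / 0.9 = 14.4 SDs apart, and d = 0.30 would be 0.27 points on a 38-point range.

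**Step 5: sensitivity to the Dutch effect, d = 0.28 (t-test power).**

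| Analysed per arm | Basis | Power |
|---|---|---|
| 175 | 20% dropout | 74% |
| 197 | about 90% retention, 0.9 × 219 | 79% |
| 219 | no dropout | 83% |

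These are for an unadjusted test. The planned mixed model includes baseline values. If 0.28 is an unadjusted post-test effect (an assumption), a baseline-to-6-week correlation of about 0.36 would bring power at 175 per arm to about 80%: 0.28 / √(1 − 0.36²) = 0.300. The protocol article gives no such correlation.

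**The case against.** The strongest defence is that this is a labelling slip in one sentence. Once 0.30 is read as a Cohen's d, 175 per arm, 80% power and 438 all hold; read literally, the trial has more power than claimed. The endpoint, test and analysis are untouched, and results will be read from the estimate and its confidence interval rather than from planning power. All of this stands. It limits the consequence, but it does not make the paragraph correct as written.

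Four stronger readings are tempting, and the protocol article does not support them.

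- *The Dutch 0.28 contradicts the 0.30.* It does not. The paragraph reports 0.28 as an observed result and then openly plans on another value, which is a design choice. The 74% power at 0.28 also depends on the full 20% dropout and an unadjusted test.
- *The trial is sized on a difference far below its own threshold of clinical significance.* The protocol says that "a pre-post difference of 6 points is considered clinically significant". That is a pre-post change, whereas the sample size concerns a difference between group means at post test. The two are not comparable targets.
- *An SD of 0.9 is impossible on this scale.* That goes beyond the text, which does not say that 0.9 is in raw Beck points; it may be on a standardised or transformed scale. The fair criticism is that the unit is missing, and that the value is hard to reconcile with the scale if it is in points.
- *The sample size is wrong and more participants are needed.* Nothing shows this. 438 is right for a Cohen's d of 0.30.

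**Conclusion.** The point holds as an error in the stated basis of the sample size, not in the number itself. As worded, SD 0.9 and a difference of 0.30 give about 142 per arm, 33 fewer than the 175 stated, and 175 per arm would have about 87% power rather than 80%. The figure of 175, and with it 438, is reproduced only with 0.30 as a standardised effect. The role and unit of the 0.9 are unexplained, so the detectable difference in Beck points cannot be read from the document.

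This rests on a two-sided 5% test, but a one-sided test does not rescue the stated inputs. That 0.9 is implausible in raw points is an inference from the scale range and the two cutoffs; no other SD is given.

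**What to change.** Keep the total at 438 and restate its basis, for example:

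> With 175 analysable participants per condition, an unadjusted two-sample t-test at the two-sided 5% level has 80% power to detect a standardised difference (Cohen's d) of 0.30 in Beck Scale for Suicide Ideation scores at 6 weeks. Allowing for 20% dropout, 438 participants will be randomized.

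Delete the SD of 0.9, or correct it and state its unit and scale. Give the SD assumed in Beck scale points, so that d = 0.30 can be read as a between-group difference in points.

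As a sensitivity statement, add that at the Dutch d of 0.28 power is about 74% with 175 analysed per arm and about 79% at roughly 90% retention, both unadjusted, and that adjustment for baseline would raise these figures.

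The cost is rewording one paragraph. The planning statement becomes slightly less favourable at the Dutch effect. No participants are added and the analysis does not change.
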